## Abstract

**Background:**

Computerised cognitive behaviour therapy (cCBT) involves standardised, automated, interactive self-help programmes delivered via a computer. Randomised controlled trials (RCTs) and observational studies have shown than cCBT reduces depressive symptoms as much as face-to-face therapy and more than waiting lists or treatment as usual. cCBT’s efficacy and acceptability may be influenced by the “human” support offered as an adjunct to it, which can vary in duration and can be offered by people with different levels of training and expertise.

**Methods/design:**

This is a two-by-two factorial RCT investigating the effectiveness, cost-effectiveness and acceptability of cCBT supplemented with 12 weekly phone support sessions are either brief (5–10 min) or extended (20–30 min) and are offered by either an expert clinician or an assistant with no clinical training. Adults with non-suicidal depression in primary care can self-refer into the study by completing and posting to the research team a standardised questionnaire. Following an assessment interview, eligible referrals have access to an 8-session cCBT programme called *Beating the Blues* and are randomised to one of four types of support: brief-assistant, extended-assistant, brief-clinician or extended-clinician.

A sample size of 35 per group (total 140) is sufficient to detect a moderate effect size with 90% power on our primary outcome measure (Work and Social Adjustment Scale); assuming a 30% attrition rate, 200 patients will be randomised. Secondary outcome measures include the Beck Depression and Anxiety Inventories and the PHQ-9 and GAD-7. Data on clinical outcomes, treatment usage and patient experiences are collected in three ways: by post via self-report questionnaires at week 0 (randomisation) and at weeks 12 and 24 post-randomisation; electronically by the cCBT system every time patients log-in; by phone during assessments, support sessions and exit interviews.

**Discussion:**

The study’s factorial design increases its efficiency by allowing the concurrent investigation of two types of adjunct support for cCBT with a single sample of participants. Difficulties in recruitment, uptake and retention of participants are anticipated because of the nature of the targeted clinical problem (depression impairs motivation) and of the studied interventions (lack of face-to-face contact because referrals, assessments, interventions and data collection are completed by phone, computer or post).

**Trial registration:**

Current Controlled Trials ISRCTN98677176

## Background

Depression is one of the most prevalent and burdensome health and social problems world-wide
[1]. Access to evidence-based psychological interventions, especially cognitive behaviour therapy (CBT), is restricted because of scarce healthcare resources and too few trained therapists
[2]. Computerised cognitive behaviour therapy (cCBT) can be used as an alternative, or as a primer, to traditional face-to-face CBT for mild-to-moderate depression within a stepped care model
[3].

A recent meta-review
[4] supported the efficacy of cCBT for depression, drawing on ten systematic reviews and numerous randomised controlled trials (RCTs) that had demonstrated that cCBT for depression can be more effective than treatment as usual
[5,6] or than a waiting list control
[7,8], and as effective as therapist-delivered face-to-face CBT
[9,10]. cCBT is generally an acceptable intervention to patients
[11,12]; however, its uptake is low and the drop-out rate can be high
[13-15]. This is common for e-health interventions
[16] and more so for open access websites and observational studies rather than for controlled trials
[17,18].

The efficacy and acceptability of cCBT may be influenced by whether, and how much, human support is offered as an adjunct to it. A meta-analysis
[19,20] found that Internet- delivered CBT was four times more effective when delivered with a supportive online therapist contact. Two further meta-analyses
[10,20] indicated that the longer the therapist input, the better the clinical outcomes with cCBT. A recently published RCT
[7] found marginally better outcomes for depression with cCBT supplemented by weekly email therapist support compared to unguided cCBT. Two other RCTs on social phobia found that cCBT with therapist guidance by email was superior to unguided cCBT
[21] and an Internet-accessed CBT self-help manual had better outcomes when supplemented by an online discussion group
[22]. Also, users of a self-help book for bulimia, albeit not computerised, improved more if they had some personalised guidance rather than none
[23,24].

The relationship between adjunct support and improved adherence or outcomes with cCBT is not always supported in the literature. Having three face-to-face support sessions with a therapist as an adjunct to cCBT for bulimia nervosa did not enhance adherence or outcomes compared to cCBT with minimal guidance
[25]. Also, weekly telephone tracking for cCBT for depression did not have an advantage over standalone cCBT
[26]. Finally, more frequent therapist contact via email (three times vs. once per week) did not improve outcomes and adherence with cCBT for panic
[27]. There is a need for further research to investigate whether keeping support sessions for cCBT for depression as brief as possible can save staff time without significantly compromising outcomes and acceptability, or whether offering longer support sessions can yield greater patient improvement or better completion rates.

Some cCBT studies
[21] use therapists who, whilst more expensive, may satisfy patients’ expectations and needs better than non-experts. Other studies use less experienced support staff, such as an administrator
[28,29], lay counsellors
[26] or psychology students
[22], who are easier to find and less costly to employ, but may be less effective or less acceptable, or may have hidden costs (for example, increased patient use of other services). Two studies
[28,29] directly compared cCBT with phone or email support from a therapist vs. an assistant and found similar symptom improvement in people with depression and generalized anxiety disorder (GAD) between the two groups. No studies have so far investigated the cost-effectiveness or explored patients’ experiences of receiving therapist vs. assistant support as an adjunct to cCBT.

This paper describes the protocol for a factorial RCT whose primary aim is to compare the clinical effectiveness, cost-effectiveness and acceptability of cCBT with two different types of support offered as an adjunct to it: brief vs. extended, and clinician vs. assistant support. To this end the study has the following primary objectives:

1. To compare clinical outcomes (depression and anxiety symptoms, functioning and quality of life) between brief and extended support for cCBT and between clinician and assistant support for cCBT.

2. To assess the cost-effectiveness of cCBT with brief vs. extended support and with clinician vs. assistant support and to estimate the cost for the National Health Service (NHS} of the population-wide implementation of the most cost-effective option.

3. To report and compare acceptability of cCBT (attrition, treatment usage and patient experiences) between brief vs. extended support and between clinician vs. assistant support.

The study also aims to evaluate the process of recruiting and screening patients with depression for cCBT, to explore effect modifiers (specifically severe vs. mild/moderate depression or anxiety, and referrals from general practitioners (GPs) vs. mental health professionals) and predictors of cCBT usage and outcomes, to indicate the most appropriate measures for assessing clinical outcomes with cCBT, and to compare the computer and the support person with respect to creating and maintaining a therapeutic alliance with the patient. To this end, the study has the following secondary objectives:

1. To compare the characteristics of referrals for cCBT who take up the offer for assessment and treatment with the characteristics of referrals who drop out before randomisation (refusals).

2. To assess whether a clinician or an assistant can reliably predict patient suitability for cCBT by reviewing patients’ written responses to a standardised questionnaire.

3. To explore whether outcomes and satisfaction with different levels of support for cCBT vary for certain sub-groups of patients (severe vs. mild/moderate depression or anxiety and referrals from GPs vs. mental health professionals).

4. To investigate whether patient characteristics and treatment group predicts clinical outcomes, number of cCBT sessions completed, and patient satisfaction.

5. To assess the similarity of various standardised self-report questionnaires for the assessment of depression, anxiety and functioning and quality of life.

6. To compare and assess the similarity of alliance ratings and explore patients’ experiences using a computerised self-help system vs. speaking to a support person on the telephone.

7. To identify common themes and key differences in the content and style of brief vs. extended support and of clinician vs. assistant support.

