#### Clinical outcomes

Work and social adjustment scale (WSAS)
[34,35]: this is a 5-item self-report questionnaire that assesses impairment of everyday functioning with scores of 0 to 40 (lower scores denote less impairment). Each item asks the patient to rate how much a particular area of their life is affected by their problem (work, social activities, private leisure activities, relationships) on a 9-point scale, where 0 represents ‘not at all’ and 8 represents ‘very severely’. This is a brief and well-validated measure that has previously been used in many studies and is part of routine data collection in the NHS Improving Access to Psychological Therapies (IAPT) Programme
[36].

We chose a generic measure of functioning instead of a symptom-specific measure for our primary outcome for three reasons: a) improved functioning is a key objective of primary care mental health services with the view of helping people return to work
[37]; b) people with depression and mixed anxiety are a heterogeneous group and c) we can establish cost-effectiveness measuring effects of functioning with both the WSAS, commonly used by clinicians, and the EQ-5D, commonly used by health economists.

Beck depression inventory (BDI)
[38]: this is a 21-item questionnaire that measures presence and severity of depression. Each item relates to a specific symptom of depression and includes four statements corresponding to scores 0, 1, 2 or 3 (higher scores, greater severity). Patients choose one of the four statements to describe the extent to which they were troubled by each symptom over the previous week. The items are then summed to obtain a total score that can range from 0 to 63 (higher total scores indicate more severe depression). Standard cut-offs are: 0 to 9, no depression; 10 to 18, mild-moderate depression; 19 to 29, moderate-severe depression and 30 to 63, severe depression.

Beck anxiety inventory (BAI)
[39]: this is a 21-item self-report questionnaire that assesses the presence and severity of anxiety. Each of its items corresponds to a common symptom of anxiety, which patients rate based on how much they were troubled by that symptom over the previous week (0, not at all; 1, mildly troubled; 2, moderately troubled and 3, severely troubled). The items are then summed to obtain a total score that can range from 0 to 63 (higher scores, greater anxiety). Common cut-off points are: 0 to 21, low anxiety; 22 to 35, moderate anxiety and over 36, severe anxiety.

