A per-protocol analysis will also be performed on the main outcomes using completers only, which we define as those patients who complete at least 5 cCBT sessions. We will compare sub-group effects by including interaction terms in appropriate linear models. We will use linear models to investigate which demographic and clinical variables predict primary outcome, session completion and patient satisfaction. Interaction terms may be included to investigate which variables modify the main effects. Secondary analysis will be carried out using the electronic data collected by the cCBT system in every session. The series of session electronic outcomes will be summarised and compared between treatment groups using repeated measures analysis.

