### Economic evaluation

To establish the cost-effectiveness of clinicians vs. assistants offering brief vs. extended support, we will combine the effects and costs of each of the four support modes (brief-clinician vs. brief-assistant vs. extended-clinician vs. extended-assistant support). Effects will be measured using both the WSAS and the EQ-5D. Cost will be estimated by assigning appropriate unit costs to resources used by patients (therapist contact time, cCBT use, medication use, GP consultations, in-patient and out-patient care, etcetera) before, during and after the interventions. All costs will be calculated in UK £ Sterling using both internal sources (for example, the relevant local organisations’ finance departments) and external sources (for example, Personal Social Services Research Unit (PSSRU)-health and social care costs
[53]). We will estimate cost-effectiveness from the perspective of the NHS and social services according to NICE guidelines
[41]) and also from a broader societal perspective (encompassing for example, patient travel costs, lost productivity and other support received).

If one support mode is shown to be less costly and more effective than all others, determining the most cost-effective support mode will be straightforward, as that support mode would dominate others. Alternatively, the incremental cost per unit of effect will be estimated for each support mode, and the resulting incremental cost-effectiveness ratio (ICER) will be assessed in relation to a range of cost-effectiveness thresholds. To characterise the level of uncertainty in decision-making based on the cost-effectiveness analysis, we will present economic data based on the cost-effectiveness acceptability curve (CEAC) and cost-effectiveness acceptability frontier (CEAF)
[54].

Additionally, sub-group analysis (severe vs. mild/moderate depression or anxiety; referrals from GPs vs. mental health professionals) will be conducted in order to assess how the costs and effects of different modes of support for cCBT vary across different patient groups. Sensitivity analysis will assess the robustness of conclusions to key assumptions that are made within the economics analysis (for example, the level of payment for clinicians or assistants employed). Finally, we will estimate the budgetary impact for the NHS of the population-wide long-term implementation of the most cost-effective mode of individualised support for cCBT.

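### Severity is named as an effect modifier only as a severe v mild/moderate split, with no instrument or cut given, although full baseline BDI and BAI scores could carry the interaction test

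*Protocol article*

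**What the plan says.** The Background states the secondary aim "to explore effect modifiers (specifically severe vs. mild/moderate depression or anxiety, and referrals from general practitioners (GPs) vs. mental health professionals". Secondary objective 3 then asks whether outcomes and satisfaction with the levels of support vary by sub-group, again giving "severe vs. mild/moderate depression or anxiety and referrals from GPs vs. mental health professionals". Severity appears in both places as two levels.

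The Statistical analysis section gives the method: "We will compare sub-group effects by including interaction terms in appropriate linear models". It adds an optional, open-ended step: "Interaction terms may be included to investigate which variables modify the main effects". Neither sentence says whether severity enters as a score or as a category.

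Clinical outcomes describes both scales as summed totals. For the BDI: "The items are then summed to obtain a total score that can range from 0 to 63 (higher total scores indicate more severe depression"). For the BAI: "The items are then summed to obtain a total score that can range from 0 to 63 (higher scores, greater anxiety"). The upper BDI bands are "19 to 29, moderate-severe depression and 30 to 63, severe depression"; the band below them, 10 to 18, is labelled mild-moderate. Data collection has the postal questionnaires completed at baseline, and the Statistical analysis section relies on baseline values of the outcome measures, so the scores are available as modifiers.

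No section states which instrument or cut-off defines severe, what share of patients is expected to be severe, or what power the severity interaction has.

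**The concern.** A single cut treats all patients on one side of it as alike. If the cut were BDI 30, a patient scoring 29 would be grouped with the mildest and a patient scoring 30 with the most severe. The Sample section sets no upper severity limit, so the range within the severe group could be wide. If the effect of support changes gradually with severity, the split discards the within-group part of that gradient, and the interaction is estimated less precisely than the data allow.

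The answer also depends on where the cut falls, and here that is open. The objective contrasts severe with mild/moderate, but the BDI band of 19 to 29 is labelled moderate-severe, so the cut could be 19 or 30. The BAI bands end at 35 and resume above 36, which leaves a score of exactly 36 unplaced. It is also unclear whether depression or anxiety means one combined split or two separate ones.

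At stake is one exploratory secondary objective. A null result from a needlessly weakened test could be misread as evidence that severity does not matter. The primary analysis is unaffected.

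**Working it through.** **Inputs from the protocol article.** Sample size section: 140 patients analysed (70 v 70 for each support factor), significance level 0.05 (taken as two-sided), WSAS SD 8.5, target main effect 0.477 SD, detectable interaction 0.961 SD at 80% power.

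**Assumptions not in the documents.** The share severe, p (shown at 0.50, 0.30 and 0.20); a roughly normal severity score; modification roughly linear in that score.

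**Step 1: reproduce the article's interaction figure.** For two balanced binary factors with 35 per cell, SE = sqrt(4/35) = 0.338 SD. With a noncentral t on 136 df, 80% power needs 2.82 × 0.338 = 0.954 SD. The stated 0.961 SD has 80.6% power, so it reproduces. A 50/50 severity split crossed with one support factor has the same standard error.

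**Step 2: the split test at other shares.** SE = sqrt(4/(140p) + 4/(140(1−p))). At p = 0.30 this is sqrt(4/42 + 4/98) = 0.369 SD.

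| Share severe | SE (SD) | Detectable at 80% power | WSAS points | Power for 0.477 SD |
|---|---|---|---|---|
| 0.50 | 0.338 | 0.95 SD | 8.1 | 29% |
| 0.30 | 0.369 | 1.04 SD | 8.8 | 25% |
| 0.20 | 0.423 | 1.19 SD | 10.1 | 20% |

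Most of this weakness comes from the sample size. Moving from 50/50 to 30/70 adds only about 0.09 SD to the detectable difference.

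**Step 3: information kept by the split.** For a normal modifier with a linear interaction, the share kept is φ(z)² / (p(1−p)), where z is the normal quantile at p.

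- p = 0.50: 0.3989² / 0.25 = 0.637, so 36% is lost
- p = 0.30: 0.3477² / 0.21 = 0.576, so 42% is lost
- p = 0.20: 0.2800² / 0.16 = 0.490, so 51% is lost

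The loss is smallest at 50/50 and symmetric about it, so 36% is the floor and 36% to 42% covers p from 0.30 to 0.70. In effective sample size, 140 becomes 89, 81 or 69. If the continuous test had 80% power, the split test would have 61%, 57% or 50%.

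**Step 4: power after the change.** Take p = 0.30 and a gradient whose severe v mild/moderate contrast is 0.477 SD. The split test has ratio 0.477/0.369 = 1.29, about 25% power. The continuous test has ratio 1.29/sqrt(0.576) = 1.70, about 39% power.

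**Step 5: sensitivity to the score distribution.** Simulated BDI-like scores cut at 30 lost 36% to 50%. Skewed BAI-like scores cut at 36 lost 40% to 60%. These distributions were assumed, not taken from the trial.

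**The case against.** The strongest defence is that an objective names populations of interest and does not specify how a covariate is coded. The Statistical analysis section never says that scores will be categorised, its optional interaction terms leave continuous scores open, and instrument and cut-off are details often left to an analysis plan, which is not shown here. This stands in part. A reader might infer that the article rules out a continuous analysis, or that it defines severe by the BDI and BAI; it does neither. But the only form in which severity is named for this objective is the two-level one, and the optional terms do not commit to anything else.

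A second defence is that the categorical question is natural. The cCBT section says the programme was recommended for mild-moderate depression, while the trial sets no upper severity limit, so how support works in severe patients is worth reporting. That also stands, and is a reason to keep the categories for description. It does not make the split the better test. If modification were a true threshold, a linear score would fit less well and the loss figures above would not apply; the article claims no threshold.

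Third, the objective is exploratory, and the test is underpowered with or without the change. That is correct and limits the importance of the point.

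**Conclusion.** The point holds as a low-cost improvement in precision for one exploratory objective. Under a roughly normal score and roughly linear modification, the split loses at least about 36% of the information, 36% to 42% if 30% to 70% are severe, and about 51% if 20% are.

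Four stronger readings are not supported:

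- **A single loss figure such as 40%.** The share severe and the score distribution are not in the documents, so only a range with its assumptions can be given.
- **That the change makes the test adequate.** For a 0.477 SD difference at 30/70, power rises only from about 25% to about 39%.
- **That recommendations on tailoring support depend on this test.** Potential implications speaks of tailoring to different patients without mentioning severity.
- **That the economic sub-group analysis is also at fault.** The Economic evaluation section repeats the split ("sub-group analysis (severe vs. mild/moderate depression or anxiety; referrals from GPs vs. mental health professionals"), but categories are serviceable for those tables and the fix leaves them as they are.

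**What to change.** In the Statistical analysis section, state that the main severity test is the interaction of each support factor with continuous baseline BDI and, separately, with continuous baseline BAI, in the linear models already planned. Add one quadratic term as a check for curvature, recognising that this check will itself have little power. Report the estimated support effect with its confidence interval at scores chosen to represent mild/moderate and severe patients. Keep the two-level categories for description and for the economic sub-group tables, and state the instrument and cut that define them, including where BDI 19 to 29 belongs.

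The cost is analysis wording only; no new data are needed. The downside is that a linear gradient is assumed, so a true threshold effect would be captured less well.

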## Methods/design

### Design

This is a two-by-two factorial RCT. Patients are randomly allocated to an eight-session cCBT programme supported either by a clinician or by an assistant, each offering either brief or extended phone support. The four randomly-created groups are: brief-clinician, brief-assistant, extended-clinician or extended-assistant support for cCBT. The primary follow-up point is at 3 months post-randomisation and the secondary follow-up point is at 6 months post-randomisation.

